On this basis, we developed the “Sleep Healthy” smartphone application to deliver digital BBT-I and paired it with wearable LT glasses to create a four-week “digital BBT-I + LT” program. A prior pilot randomized controlled trial (RCT) in university students demonstrated greater reductions in Insomnia Severity Index (ISI) scores and a shift toward morningness in the intervention group [8], but external validity remains to be established.

The present study, therefore, conducts a three-arm RCT comparing digital BBT I + LT, digital BBT I alone, and a waitlist control to evaluate efficacy in young adults with evening-type chronotypes. We primarily hypothesized that young adults with insomnia and late chronotypes in the digital BBT-I groups would achieve significantly greater reductions in ISI scores from baseline to post-test than the waitlist control group. Furthermore, we hypothesized that: (1) digital BBT-I with LT groups would show a significant significantly greater reductions in ISI scores from baseline to post-test than the waitlist control; (2) intervention groups would show a significant shift toward morningness (Morningness–Eveningness Questionnaire [MEQ] scores) by the post-test; (3) these groups would exhibit improved daytime sleepiness (Epworth Sleepiness Scale [ESS]), sleep health (Ru-SATED), depressive symptoms (Patient Health Questionnaire-9 [PHQ-9]), and sleep knowledge by the post-test; and (4) clinical gains would be sustained at the 3-month follow-up. The findings of this study are expected to contribute to the development of new prevention and treatment strategies for sleep-related problems among young adults.

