### 2.7. Outcome Measures

The primary outcome of the protocol was the change in insomnia symptoms, as measured by the ISI. The ISI was measured at baseline (T_1_), once a week during the intervention (on days 8, 15, and 22), post-test (day 29) (T_post_), and again at the 3-month follow-up (T_3 month_).

The secondary outcomes were assessed using the MEQ, ESS, Ru-SATED, PHQ-9, sleep quiz, and other measures. They were measured at baseline, post-test (day 29), and at a 3-month follow-up.

Figure 1 shows a synopsis of all the outcome measures and assessment time points.

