### 3.2. Analysis

For the primary outcome (ISI), longitudinal data were analyzed using linear mixed-effects models with random intercepts to account for repeated measurements and individual variability. The fixed effects in the model included the treatment group, five time points (baseline and weeks 1–4), and the group-by-time interaction term. Secondary outcomes were compared using independent-samples *t*-tests to evaluate mean changes from baseline to post-test and 3-month follow-up. Harms and baseline covariates were summarized using descriptive statistics.

The analysis included all participants randomized according to their assigned groups. The use of linear mixed-effects models allowed the inclusion of all participants who provided at least some follow-up data, thus ensuring a robust assessment of the effectiveness of the intervention.

Missing data were handled using linear mixed-effects models, which automatically perform imputation based on available longitudinal data. This approach accounts for participants who may discontinue the intervention, while still allowing their available weekly measurements to contribute to the overall analysis.

While the primary focus is on the main hypotheses, subgroup analyses may be conducted if qualitative reviews suggest that specific patient subgroups, defined by demographic characteristics, differences in app engagement data, or variations in alliance [26], exhibit differing patterns of response to treatment.

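### Secondary outcomes are tested with t-tests on change that use only participants seen at the later visit, and 3-month ISI, needed for hypothesis (4), is in no stated analysis

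*Protocol article*

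**What the plan says.** Section 3.2 gives ISI a linear mixed model with random intercepts, whose fixed effects are group, "five time points (baseline and weeks 1–4), and the group-by-time interaction term". For the rest, "Secondary outcomes were compared using independent-samples" t-tests "to evaluate mean changes from baseline to post-test and 3-month follow-up".

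Section 2.7 measures ISI weekly, at day 29 "and again at the 3-month follow-up". It lists the secondary outcomes as MEQ, ESS, Ru-SATED, PHQ-9, the sleep quiz and other measures. Of these it says: "They were measured at baseline, post-test (day 29), and at a 3-month follow-up". ISI is not in that list.

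Hypothesis (4) in the Introduction is that "clinical gains would be sustained at the 3-month follow-up".

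Section 3.2 also states: "The analysis included all participants randomized according to their assigned groups". It then says that mixed models handle the missing data, and that weekly values from people who stop the intervention still contribute. Section 3.3 places the missing-at-random assumption and the intention-to-treat framework under the primary analysis, and applies Holm to the secondary outcomes.

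**The concern.** There are three linked issues.

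1. **Test for the secondary outcomes.** A two-sample t-test on change needs both values. Anyone without the later visit drops out, and no imputation is stated for these outcomes. Someone seen at day 29 but not at 3 months contributes nothing to the 3-month comparison, although the day-29 value is informative.
2. **3-month ISI.** The visit is collected, yet the mixed model excludes it by its stated time levels, and the t-tests are assigned to outcomes that do not include ISI. The test of durability for the main clinical outcome could then be chosen after the data are seen.
3. **Scope of the missing-data sentences.** The statements on all randomised participants and on mixed-model handling carry no restriction, but they describe only the ISI model.

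At stake are the precision of the secondary results, their protection against dropout related to response, and a prespecified test of ISI durability. The first matters in a trial of 30 per arm with Holm correction. The second matters because participants know their arm and the comparator is a waitlist.

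**Working it through.** **Inputs from the article.** 30 per arm; d = 0.80; 80% power; two-sided α = 0.05; 20% attrition to the post-test (Section 3.1); MEQ entry range 16–41 (Section 2.3). No 3-month retention is stated. Correlations, SD ratios and dropout mechanisms below are assumptions.

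**The plan's own figure.** n = 2(1.960 + 0.842)² / 0.80² = 24.5, so 25 per arm. 25 × 1.2 = 30 per arm, 90 in total, as stated. Nothing in this point changes that figure.

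**Participants not used.** 30 × 0.20 = 6 per arm have no post-test value. The loss at 3 months is unknown. At assumed retention of 80%, 70% or 60%, the t-test would use 24, 21 or 18 per arm.

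**Precision.** Let the follow-up SD be 1, the baseline SD k and their correlation ρ.
- Variance of change: 1 + k² − 2ρk.
- Variance after baseline adjustment: 1 − ρ².
- Difference: (k − ρ)², which is never negative. In large samples the t-test on change therefore cannot be more precise.
- With equal variances (k = 1) the ratio of adjusted to change-score variance is (1 − ρ²)/[2(1 − ρ)] = (1 + ρ)/2.

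| k | ρ | Adjusted / change-score variance |
|---|---|---|
| 1.0 | 0.3 | 0.65 |
| 1.0 | 0.5 | 0.75 |
| 1.0 | 0.7 | 0.85 |
| 0.8 | 0.5 | 0.75/0.84 = 0.89 |
| 0.6 | 0.5 | 0.75/0.76 = 0.99 |
| 0.6 | 0.7 | 0.51/0.52 = 0.98 |

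The last rows matter for MEQ, because restricting entry to 16–41 probably compresses its baseline SD.

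**Bias from using only those with the later value.** A large simulation (600,000 per arm) took a true 3-month effect of −0.50 SD. Waitlist dropout was at random. Treated-arm dropout was more likely with poor observed response, driven either by the day-29 level or by the change to day 29. Correlations (baseline–day 29, day 29–3 months, baseline–3 months) were 0.5, 0.7, 0.4 or all 0.6.

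| Dropout driven by | Dropout | Contrast, 0.5/0.7/0.4 | Contrast, all 0.6 |
|---|---|---|---|
| Day-29 level | 20% | −0.54 | −0.50 |
| Day-29 level | 30% | −0.55 | −0.50 |
| Change to day 29 | 20% | −0.64 | −0.57 |
| Change to day 29 | 30% | −0.70 | −0.61 |

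An estimate that also uses the baseline and day-29 values of participants missing at 3 months stayed at −0.50 throughout. The bias of the t-test contrast thus ran from 0 to 0.20 SD, in the direction that favours treatment.

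**3-month ISI.** Set side by side, Section 2.7 collects it, Section 3.2 leaves it out of the mixed model, and the t-tests apply to a list without ISI. Neither stated analysis covers it.

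**The case against.** The strongest reply is that the missing-data text was never meant for the secondary outcomes. It refers to weekly measurements, only ISI is weekly, and Section 3.3 ties missing at random and intention-to-treat to the primary analysis. This largely stands. A reader might infer that the article contradicts its own intention-to-treat commitment. The documents support less: the sentences in Section 3.2 are unrestricted where they should be restricted.

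Other objections that stand:
- A t-test on change is valid under randomisation without missing data, and subtracting baseline does not ignore it.
- Omitting the stratification factors is not peculiar to the t-tests. The ISI model as described omits them too.
- Dropout that depends on arm alone does not bias the contrast, because completers are then a random subset of each arm.
- People lost before day 29 have only a baseline value for the secondary outcomes, so a new model gains almost nothing from them.
- If dropout follows interim ISI, a model of MEQ or PHQ-9 alone would not remove the bias.
- Heavier loss by 3 months is plausible but not stated.

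It can also be said that an article may leave follow-up analyses to an analysis plan that is not shown. That does not dispose of the ISI point, because the article itself fixes the five time levels and assigns the t-tests to a named list.

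**Conclusion.** The point holds in a limited form. The secondary t-tests use only participants with the later value, make no use of day-29 data for people missing at 3 months, and are at best as precise in large samples as a baseline-adjusted analysis. 3-month ISI has no stated analysis, although hypothesis (4) needs it. The all-randomised and missing-data sentences fit only the ISI model.

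The size depends on assumptions. With equal variances the adjusted variance is 0.75 or 0.85 of the change-score variance at ρ = 0.5 or 0.7, equivalent to 1/0.75 = 1.33 or 1/0.85 = 1.18 times the participants. This must not be carried over to MEQ, where the gain may be near nil. Bias was 0 to 0.20 SD under the assumed mechanisms and requires dropout related to outcome.

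Two stronger readings should be avoided. The article does not show that the secondary results will be biased. Nor is durability wholly untested: the listed secondary outcomes have a stated 3-month comparison, and the gap is for ISI. The change is worth making because it is cheap and uses data already planned, but the validity of the primary analysis does not depend on it.

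**What to change.** 1. **Secondary outcomes.** Replace the t-tests by a baseline-adjusted repeated-measures model for each outcome, with day 29 and 3 months as responses, arm-by-time, sex and baseline ISI stratum. Report each intervention arm versus waitlist at both visits, with Holm applied to those contrasts.
2. **Dropout linked to interim ISI.** If this is thought possible, bring in observed ISI as an auxiliary variable, for example by multiple imputation.
3. **ISI.** Add 3 months as a sixth time level, or specify a separate follow-up model. Keep day 29 primary. For hypothesis (4), report the 3-month contrast versus waitlist together with the within-arm change from day 29 to 3 months, because a contrast with waitlist alone does not show that a gain was sustained.
4. **Wording.** If the secondary analyses stay as they are, limit the all-randomised and missing-data sentences in Section 3.2 to the primary ISI analysis, and still name the 3-month ISI analysis.

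The cost is a change of wording in the article and analysis plan, a little programming and a slightly more complex model. No new data are needed.

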### 3.3. Additional Statistical Considerations

Multiplicity: Multiplicity adjustment will not be applied to the single prespecified primary outcome. Secondary outcomes will be adjusted using the Holm procedure. Model assumptions and convergence were assessed using standard diagnostic procedures, including residual and Q–Q plots.

Missing data and sensitivity analyses: The primary analysis will use linear mixed-effects models under the missing-at-random assumption within an intention-to-treat framework. Sensitivity analyses will include per-protocol analyses and alternative covariance structures to assess robustness.

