## Abstract

**Background:** Insomnia symptoms associated with late chronotypes are prevalent among young adults, and frequently lead to sleep deprivation, morning-awakening difficulties, and excessive daytime sleepiness. These conditions are associated with psychological distress, impaired academic functioning, and reduced self-esteem. Although chronobiological behavioral interventions are effective, their accessibility remains limited. To bridge this gap, we developed a smartphone application delivering digital brief behavioral treatment for insomnia (BBT-I). We also designed a four-week program integrating the app with light therapy (LT) via wearable glasses named “Digital BBT-I + LT”. This randomized controlled trial will evaluate the efficacy of digital BBT-I with LT and digital BBT-I alone compared with a waitlist control group. **Methods:** This three-arm parallel-group randomized controlled trial will target young adults with insomnia symptoms and late chronotypes. Participants will be randomized to receive digital BBT-I with adjunctive LT, digital BBT-I alone, or a waitlist control condition. The primary outcome will be insomnia symptom severity, assessed using the Insomnia Severity Index. Evaluations will be conducted at baseline, weekly during the four-week intervention period (days 8, 15, 22, and 29), and at the 3-month follow-up. **Discussion:** Late chronotypes and insomnia significantly impair sleep and mental health in young adults. Despite the recognized importance of chronobiology-based treatments, they are rarely adopted as standard care. This highlights the need for scalable digital interventions, such as digital BBT-I. By rigorously assessing these strategies, this trial aims to provide clinical evidence regarding accessible interventions to improve sleep and mental health outcomes in this population.

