## 3. Statistical Analysis

### 3.1. Sample Size

Sample size calculations were informed by the results of our pilot study [8] and the existing literature [25]. The pilot study, which utilized digital BBT-I + LT, demonstrated a large effect size on ISI scores (*d* = 1.080; 95% CI: 0.226–1.914). Additionally, a network meta-analysis reported a moderate effect size for digital CBT-I (*d* = −0.78; 95% CI: −1.18, −0.38) [25]. Based on these findings, we conservatively estimated a medium-to-large effect size of *d* = 0.80 for the comparison of digital BBT-I against the waitlist control.

To detect this effect size with 80% power and a two-sided α = 0.05, a total sample of 90 participants (30 per group: digital BBT-I + LT, digital BBT-I, and control) was required. This target sample size accounted for an estimated 20% attrition rate (i.e., 80% retention), ensuring that at least 25 participants per group would complete the post-test assessment.

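### The multiplicity waiver rests on having one primary outcome, but that outcome carries two comparisons with a shared waitlist and no success rule; if either may win at 0.05, the false-positive risk is about 9.1%

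*Protocol article*

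**What the plan says.** All of this is in the protocol article.

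- **Section 3.3:** "Multiplicity adjustment will not be applied to the single prespecified primary outcome". The next sentence reads "Secondary outcomes will be adjusted using the Holm procedure", so error control exists but is confined to secondary outcomes.
- **Abstract:** the trial is to "evaluate the efficacy of digital BBT-I with LT and digital BBT-I alone compared with a waitlist control group".
- **Section 1 (Introduction):** the primary hypothesis is that participants "in the digital BBT-I groups would achieve significantly greater reductions in ISI scores from baseline to post-test than the waitlist control group". The word for the arms is plural. Further hypothesis (1) then states BBT-I + LT versus waitlist separately, on the same outcome over the same interval.
- **Section 3.1:** the effect size of 0.80 is set "for the comparison of digital BBT-I against the waitlist control", which is one pairwise comparison, at an undivided two-sided 0.05.
- **Section 3.2:** the primary model has group, five time points and their interaction. No contrast, order, gate or success rule is stated.

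**The concern.** The reason given for the waiver does not fit the design. A single outcome removes multiplicity across outcomes, but not across arms compared with the same control on that outcome. Nor does the Holm rule reach the second arm, because it covers secondary outcomes and the second comparison is also on the ISI.

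The sections also point to different primary tests. The Abstract gives both arms. The Introduction gives the groups in the plural and then one arm again. The sample size gives one arm. With no success rule, the choice between one arm, either arm, both arms and the arms pooled could be made after the results are known. The efficacy claim could then carry a higher error rate than the 0.05 in the sample size section, while the secondary outcomes are held to a stricter standard than the primary.

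**Working it through.** **Inputs.** Allocation 1:1:1 (section 2.6). Two-sided alpha 0.05, 80% power, d = 0.80, 30 randomized and at least 25 completers per arm, 20% attrition (section 3.1).

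**1. The plan's own figure.** For a two-sample comparison of means, n per arm = 2(1.96 + 0.842)² / 0.80² = 24.5, so 25. Then 25 × 1.2 = 30 per arm and 3 × 30 = 90 in total. The stated numbers come from a single pairwise comparison at an undivided 0.05, with no allowance for a second one.

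**2. Correlation of the two contrasts.** With equal arms and a shared control, each contrast has variance 2σ²/n and their covariance is σ²/n, so the correlation is 0.5.

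**3. Error rate when neither arm works, by reading of the text.**

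| Reading | Chance of a false primary claim |
|---|---|
| Each arm at 0.05, either success counts | 9.07% (bivariate normal, correlation 0.5) |
| Both arms must succeed | 0.05 + 0.05 − 0.0907 = 0.9%; at most 5% if only one arm works |
| Arms pooled against waitlist | 5% |
| One comparison is the sole primary | 5% |

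Simulated t-tests (1,000,000 runs) agree with the first row: 9.0% at 25 per arm and 9.0 to 9.1% at 30. For reference, independent tests would give 1 − 0.95² = 9.75%, and the upper bound is 10%.

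**4. Power after a remedy.** Two-sample t-tests, d = 0.80 in both active arms:

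| | 25 completers per arm | 24 completers per arm |
|---|---|---|
| No adjustment, each contrast | 79% | 77% |
| Holm across the two, each contrast | 75% | 73% |
| Fixed sequence, first contrast | 79% | 77% |
| Fixed sequence, second contrast | 68% | 65% |
| Bonferroni (0.025 each) | 70% | 67.5% |

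The second contrast in a fixed sequence succeeds only if both are significant at 0.05, which is why its figure is the lowest. The 24 column is shown because 30 × 0.8 = 24, while section 3.1 states 25.

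**The case against.** **The two tests at 0.05 are not written down.** This is correct. Section 3.2 names one model and no pairwise test or level. The 0.05 per contrast is inferred from the sample size and the waiver. A reader might infer that the plan declares each arm tested at 0.05 with either success sufficient, and so has a fixed 9% error. The documents do not say so, and three other readings keep the primary claim at or below 5%.

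**The Introduction can be read as ranking the arms.** BBT-I + LT comes second, as a further hypothesis, and only BBT-I alone is powered. That reading is possible, but the plural in the primary hypothesis works against it. Even if it is accepted, nothing makes the second comparison depend on the first, and it falls outside the Holm family.

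**Distinct treatments in one trial may not need joint control.** This is debated in general. It is weak here: both arms receive the same app programme, share one control group and serve one primary hypothesis. The article does not argue it either; it relies on the single outcome.

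**An unseen analysis plan may settle the contrasts.** It may. The absence of contrast detail, including the fact that the overall interaction has (3 − 1) × (5 − 1) = 8 degrees of freedom, is therefore not counted as an error. What remains is the waiver, which the article states and which any testing rule elsewhere would have to be reconciled with.

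**Conclusion.** The point stands in a limited form. The waiver's reason does not cover the two comparisons with the waitlist that the article sets, and the article does not fix which result counts as primary success. Depending on the reading, the chance of a false primary claim when neither arm works runs from below 5% to about 9.1%.

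The 9.1% assumes equal arms, two-sided 0.05 per contrast, either success sufficient, and no effect in either arm. If one arm works, the error for the other is 5%. A figure of about 12% for three pairwise tests is also tempting, but the article states no hypothesis for BBT-I + LT versus BBT-I, so it does not apply.

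The power figures rest on completer t-tests. The mixed model's power would differ with the correlation between repeated ISI scores, which the article does not give.

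**What to change.** In section 3.2, name two one-degree-of-freedom contrasts from the mixed model: the difference in ISI change from baseline to day 29 for digital BBT-I versus waitlist, and for digital BBT-I + LT versus waitlist.

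In section 3.3, replace the waiver with a rule that holds their joint error at two-sided 0.05. Either of these will do:

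- **Holm across the two contrasts**, the procedure already used for secondary outcomes. No order is needed.
- **A prespecified fixed sequence**, each contrast at 0.05, the second confirmatory only if the first is significant. The order must be written down. Section 3.1 sizes the trial on BBT-I alone, whereas its pilot evidence is for BBT-I + LT, so the order needs a stated reason.

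Report BBT-I + LT versus BBT-I as an estimate with a 95% confidence interval, outside the confirmatory family. Align the hypothesis wording in the Introduction. Make the change before the blinded analyst learns group assignments.

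**Cost.** A few sentences and no added participants. Holm costs about 4 percentage points of power per contrast. A fixed sequence costs the first contrast nothing and the second about 11 points (79% to 68%) at 25 completers, and leaves the second exploratory if the first fails.

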## 4. Discussion

Insomnia symptoms associated with late chronotypes are prevalent among young adults, and when left untreated or inadequately managed, they can lead to significant functional impairments. Therefore, it is critical to investigate the efficacy of interventions for insomnia related to delayed sleep–wake phases in this population. In addition to alleviating insomnia symptoms, such interventions have the potential to enhance overall sleep and mental well-being.

Although the efficacy of chronobiological behavioral treatments is well recognized [6], access to these interventions remains limited. Leveraging digital technology to expand the reach of these treatments could provide direct support to young adults and improve their overall well-being. This clinical trial aimed to evaluate two approaches to care for young adults experiencing insomnia with late chronotypes: digital BBT-I combined with LT using light glasses and digital BBT-I alone. Ultimately, this study aimed to generate new insights and clinical guidelines, providing evidence-based support for young adults struggling with sleep-related issues.

This study has several limitations. First, a questionnaire was used to assess insomnia symptoms and late chronotypes. Future clinical studies should be conducted in participants who meet the clinical diagnostic criteria for DSWPD, especially when the application is intended for use in medical settings. Second, because the study was conducted at a single university—even though it is a large institution—the characteristics of the participants may have been biased. To enhance generalizability, additional multicenter studies will be necessary. Third, due to the nature of the active behavioral components (digital BBT-I and LT), blinding participants and site investigators was not feasible, introducing the possibility of performance and measurement bias. We addressed these concerns through several methodological safeguards. To mitigate performance bias, the “Sleep Healthy” app provided a fully automated and standardized intervention flow, minimizing human contact and reducing the risk of undue investigator influence that can occur in face-to-face therapy. To address measurement bias, the primary outcome analysis was conducted by a statistician who was blinded to group allocation and had no involvement in participant recruitment or intervention delivery. While self-reported measures such as the ISI are susceptible to expectancy effects, their standardized format and established sensitivity to change help maintain consistency across groups. Moreover, there is a growing consensus among sleep researchers regarding the importance of subjective outcomes in sleep assessment.

